### Quantitative Study Population

This study’s cohort will include patients who receive care for SUD. Eligible patients are adults aged 18 years and older with an incident SUD identified between January 1, 2017, and May 31, 2025. We will include both group practice enrollees, who receive most of their care from internal KPWA-owned and operated clinics, and KPWA health insurance plan enrollees who primarily receive care outside the internal delivery system (IDS). Incident SUD is defined as meeting any of the following criteria at a clinical encounter with no prior SUD indicators in the past 6 months: (1) a newly documented SUD diagnosis, or (2) two or more *DSM-5* (*Diagnostic and Statistical Manual of Mental Disorders, Fifth Edition*) symptoms reported on standardized patient symptom checklists. The index date will be the date of the qualifying incident SUD event. The 6-month “washout period” is used to define new treatment, modeled on National Committee on Quality Assurance definitions [36], but we may explore the sensitivity of sample definitions using other time frames, such as 60 days [37]. For patients who have been enrolled in KPWA for less than the length of the washout period, we will consider their first SUD event to be an incident SUD event. Provisionally, multiple qualifying incident SUD events from the same patient will be included in the analysis (see details in Statistical Analyses). Patients will be excluded from the analyses if they have opted out of research participation with the health plan (≈0.2%).

The analytic sample will be split into distinct study subcohorts comprising patients with incident SUD identified in the specific clinical settings. We anticipate using five subcohorts, including: (1) primary care, (2) urgent care, (3) ED or hospital, (4) behavioral health, and (5) all other settings. These locations are identified based on EHR and insurance claims data that code clinic departments, places of service, encounter types, and SUD diagnosis data available in each location (Table 1). Once patients are identified as having an incident SUD and meeting the inclusion criteria described above, they enter the initial state of the MSM.

**Table 1. T1:** Study subcohorts defined by the clinical setting in which an incident substance use disorder event occurs. Incident SUD^a^ events are identified for adult patients aged 18 years and older and are categorized into 1 of the 5 subcohorts in this table.

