### States for the MSMs

States will capture 3 types of events related to SUD care: initial states, transient states, and terminal states. Defining states requires a balance of specificity to produce actionable information, and parsimony to allow for an estimable statistical model with accurate estimates and smaller SEs.

Initial states in the MSMs represent the clinical settings that triggered an incident event at the start of an SUD care episode, corresponding to the 5 subcohorts in Table 1.

There are 3 types of transient states. The first type is care states, which include different types of care provided in the health care system to treat the SUD, defined by combinations of setting and service type (Table 2). We opted to define 15 preliminary SUD care states based on a combination of 3 settings and 5 service types. The second type of transient state is temporary discontinuation of care. Entry into the temporary discontinuation care state is triggered using a clinically meaningful threshold for time elapsed between SUD treatment visits. The last transient state is SUD remission, which represents an improvement in the patients’ disease.

**Table 2. T2:** Transient states and terminal states are represented in the multistate models.

Category	States included	Description
Transient states	A total of 17 transient states include 15 care states derived from crossing 5 service types with 3 care settings; temporary discontinuation of SUD^a^ care; and remission of use disorder.	Care states Service types Evaluation and assessment Behavioral treatment and counseling Prevention, education, and case management Pharmacotherapy Other service Settings Outpatient Intensive outpatient Inpatient or residential Other transient states Discontinuation of SUD care A lack of SUD care over a specified period^b^ Remission of use disorder Low risk score on alcohol and substance use screen; clinically meaningful reduction on screening scores or <2 symptoms on *DSM-5*^c^ checklist; SUD remission diagnosis
Terminal states	4 states representing the end of a care episode	Death, derived from dates in health care enrollment records or Washington State death data Loss to follow-up, defined as at least 31 days without KPWA insurance coverages Ceased SUD care (no medication fills or services with a qualifying SUD diagnosis for more than 194 days Administrative censoring (in the middle of a care episode when data collection ends)

a SUD: substance use disorder.

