b Temporary discontinuation will be defined separately for each care state using an appropriate threshold for time elapsed between visits that reflects acceptable gaps in care for that specific state. All of these periods will be shorter than 194 days to distinguish temporary discontinuation from ceasing substance use disorder care.

c *DSM-5*: *Diagnostic and Statistical Manual of Mental Disorders, Fifth Edition*.

Terminal states indicate the end of an SUD care episode (Table 2), such as ceasing SUD care.

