### Statistical Analyses

#### Aim 1: Apply MSMs to Comprehensively Characterize SUD Care Transitions

Separate MSMs will be run for each of the 5 subcohorts specified in Table 1. The 5 subcohorts are mutually exclusive. All prespecified states that are anticipated will be considered. States may be collapsed to address states with a small number of events, and new states may emerge if they occur with sufficient frequency (eg, concurrent receipt of pharmacotherapy and behavioral treatment and counseling). When collapsing or expanding states, we will strike a balance between clinical interpretability and reliable parameter estimation. As a general guideline, ≥40‐50 transition events from *S*_*j*_ to *S_j_* per covariate helps ensure stable hazard ratio estimates and corresponding SEs, but if collapsing states compromises the clinical interpretability of the results, we will adopt a more permissive threshold of at least 10 transition events per covariate for modeling [58]. This criterion will first be applied to define states; specifically, a minimum of 40 (or 10 under the more permissive threshold) transition events is required to define a state, allowing inclusion of 1 covariate in the transition model. When transitions are sufficient to include covariates in the model, at least 40 × *m* transition events are required. Covariate selection for each transition model, given the number of transitions, is described below. Follow-up time or care episode duration is defined as the interval from entry into the initial state (time 0) to entry into a terminal state.

Figure 1 provides a graphical representation of a simplified MSM illustrating potential care pathways. In this example, patients who meet the inclusion criteria and are identified as having an incident SUD in primary care enter the initial state *C*_1_. Patients then transit into 1 of 15 care states (*S*_1_, ... ,*S*_15_) defined by a service type and setting. From these states, patients may transition to temporary discontinuation of care, *D*, or an SUD remission state, *R*. Transitions between the transient states (care states, temporary discontinuation, and SUD remission) are bidirectional, whereas any transition to a terminal state (*T*_1_, ..., *T*_4_) is unidirectional, reflecting that patients cannot leave terminal states once they are entered in MSMs. At the end of follow-up, patients occupy 1 of the 4 terminal states.

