For simplicity, we omit transition-specific subscripts for the parameters $\left(\eta ,k_{0},\beta \right)$. In the model, $s(\log(t)|\eta ,k_{0})=\sum_{i=1}^{k_{0}}\eta_{i}B_{i}(\log(t))$ represents the log cumulative baseline intensity function, which we model flexibly using restricted cubic spline basis functions (also known as natural cubic splines) $B_{i}(\cdot )$, with corresponding coefficients $\eta_{i}$. The number of knots, $k_{0}$, determines the number of basis functions and thus the flexibility of the baseline intensity functions. For covariates *z*_*i*_(*t*), the coefficients β represent the log hazard ratios at time t. The unknown parameters to be estimated or selected from data are $\left(\eta ,k_{0},\beta \right)$. We will use the Akaike information criterion based on data to select the number of knots, with lower Akaike information criterion values indicating better model fit. The regression coefficient parameters (η,β) will be estimated by using the maximum likelihood approach for statistical inference [62,63]. For each transition, we will include prespecified covariates for adjustment when the number of transitions allows (at least 10 transition events per covariate), and if additional covariate selection is required, variables that are statistically significant at the 5% level based on Wald tests will be included [64]. The estimated transition intensities are transformed to a transition probability from states j to k at time t since entry into state j at time s (s<t, s and *t*>0), by integrating, $p_{jk}(s,t)=\exp\left\{-\int_{s}^{t}q_{jk}(u,z(u))\;du\right\}$.

Multiple incident SUD events may be observed within the same patient (see Quantitative Study Population). For example, a patient may have an incident SUD event, eventually experience a terminal state such as ceasing SUD care (eg, one who receives no SUD care for 194 days), and then experience a second incident SUD event. Including multiple incident events from the same patient within the same subcohort in the MSM framework may introduce within-patient correlation and reflect care pathways that differ from those of the initial episode. We will account for within-patient correlation using a sandwich variance estimator for the parameter estimates. The number of prior incident events will be included as a covariate or used as a stratification factor, depending on its distribution.

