How does the probability of occupying a given care state or terminal state vary over time? We will describe how the probability of occupying a state varies over time since cohort entry. To address this question, we will construct a stacked plot in which the y-axis represents the probability of being in each state, the x-axis shows time since cohort entry, and the stacked bands correspond to different states (Figure 2). Depicting the timing and probability of occupying states can help inform quality improvement interventions. For instance, by visualizing the time at which the probability of ceasing SUD care increases, it can help guide the timing of interventions to check for SUD care engagement and outreach to re-engage patients when needed.

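### The terminal state for ceased SUD care does not require that care ever began, so ceased-care results counted from cohort entry pool never-starters with drop-outs

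*Protocol article*

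**What the plan says.** The section Quantitative Study Population opens by saying that the "cohort will include patients who receive care for SUD". The entry rule that follows, and Table 1, ask only for identification: a new SUD diagnosis, or two or more checklist symptoms (diagnosis only in the emergency department or hospital subcohort). The section then states: "Once patients are identified as having an incident SUD and meeting the inclusion criteria described above, they enter the initial state of the MSM".

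The section States for the MSMs (Table 2) lists four terminal states: death, loss to follow-up, administrative censoring, and "Ceased SUD care (no medication fills or services with a qualifying SUD diagnosis for more than 194 days". The same section says of the shorter gaps: "Temporary discontinuation will be defined separately for each care state". No such threshold is given for the initial state.

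Under Aim 1 of Statistical Analyses, the only route written out of the initial state is "Patients then transit into 1 of 15 care states", and the episode closes with "At the end of follow-up, patients occupy 1 of the 4 terminal states". The transition-intensity matrix has 21 states, 17 transient and 4 terminal. Neither that count nor the index list beside it contains the initial state.

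Under Aim 2, the occupancy plot runs from cohort entry. The article says that seeing when ceasing rises can help "guide the timing of interventions to check for SUD care engagement and outreach to re-engage patients when needed".

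**The concern.** Failure to start care and failure to stay in care are different problems with different remedies: referral or outreach at identification for the first, retention in treatment for the second. If both end in one terminal state, a ceased-care percentage or curve counted from cohort entry does not show which has occurred. The Aim 2 text on the occupancy plot speaks of re-engaging patients, and the caption of the hypothetical Figure 2 speaks of maintaining engagement. Neither fits a patient who never engaged.

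This reaches declared outcomes. Study Outcomes names the percentage reaching a terminal state, and the time taken, as one of the study's two outcome types.

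**Working it through.** **State count.** 5 service types × 3 settings = 15 care states. Adding temporary discontinuation and remission gives 17 transient states, and adding 4 terminal states gives 21. This reproduces the article's figure. Neither the initial state nor a never-started state is among the 21.

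**Where a never-starter goes.** Take a patient identified in primary care by checklist symptoms who receives no SUD service or medication fill afterwards.
- Care states: never entered, by construction.
- Temporary discontinuation: its thresholds are set per care state, so none applies.
- Remission: Aim 1 describes it as reached from care states. It is also transient, so it does not close the episode.
- Death, loss to follow-up, administrative censoring: do not apply if the patient is alive, enrolled and observed for more than 194 days.
- Ceased SUD care: the 194-day condition is met, and nothing in the definition excludes the patient.

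Only the last state fits. This is an inference by elimination; the article does not state the routing.

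**Which outputs pool the two groups.**

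| Output | Starts from | Pools? |
|---|---|---|
| Survival plot for not ceasing care (Table 4) | index event | yes |
| Stacked occupancy plot (Aim 2, Figure 2) | cohort entry | yes |
| Terminal-state percentages and times (Study Outcomes) | cohort entry | yes |
| 1-year comparison across patient subgroups (Aim 2) | cohort entry | yes |
| Restricted mean survival time (Table 5, Figure 4) | entry to a care state | no |
| Transition and hitting probabilities into care states (Table 4) | initial state | no; these measure starting |
| Initiation quality measures (Aim 2) | incident event | no; these measure starting |

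**Illustration of size.** Let p be the share who never start (assumed; not in the article) and d the drop-out among starters. Set d = 0.30, the background drop-out figure in the Introduction, used only for illustration. Competing terminal states are ignored.

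Pooled ceased = p + (1 − p) × d. Never-starter share of ceased = p ÷ pooled ceased.

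| p | Pooled ceased | Never-starter share |
|---|---|---|
| 0.10 | 0.10 + 0.90 × 0.30 = 0.37 | 27% |
| 0.20 | 0.20 + 0.80 × 0.30 = 0.44 | 45% |
| 0.40 | 0.40 + 0.60 × 0.30 = 0.58 | 69% |
| 0.60 | 0.60 + 0.40 × 0.30 = 0.72 | 83% |
| 0.80 | 0.80 + 0.20 × 0.30 = 0.86 | 93% |

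One pooled value can come from very different mixes. A figure of 58% results from p = 0 with d = 0.58, p = 0.20 with d = 0.475, p = 0.40 with d = 0.30, or p = 0.50 with d = 0.16. Ceased-care occupancy from cohort entry therefore cannot by itself separate the two failures.

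**The case against.** The strongest reply is that the plan already measures the two failures apart. Initiation is a separate quality measure; hitting probabilities and first-passage times describe whether and when care is reached; Figure 3 plots not reaching a care state by initial setting; restricted mean survival time begins at care-state entry; and each transition has its own model. This stands. A reader might infer that the study cannot tell failure to start from failure to retain, and the article does not support that. The problem is confined to the outputs marked as pooling above. Separation by origin state also needs the initial state in the matrix, and the 21-state description leaves it out.

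Second, the routing is nowhere written down. A reader might take the example of repeat episodes under Aim 1, in which a patient may "eventually experience a terminal state such as ceasing SUD care (eg, one who receives no SUD care for 194 days"), as confirmation. It is not: the example does not say whether care came between the incident event and the terminal state. The case rests on elimination alone.

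Third, a reader might infer that the 1-year comparison would rank clinical settings wrongly. That comparison is made within a subcohort, across patient subgroups such as SUD type. The algebra applies to any groups that differ in initiation, but no ranking of settings by this analysis is planned.

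Fourth, a reader might argue that never-starters distort the timing of the ceased-care curve around day 194. The article does not say whether ceasing is dated at the last service or when the gap is completed. In the latter case treated drop-outs carry the same lag, so the effect is not peculiar to never-starters.

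Fifth, later visits coded with an SUD diagnosis may count as evaluation or other service, which narrows the never-started group. The article also calls its care states preliminary, allows new states to emerge, and acknowledges that other states may matter. These points lower the weight of the concern, but they do not commit the plan to separating the two groups.

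**Conclusion.** The point holds in a limited form. Ceased SUD care, as defined, admits patients who never entered a care state, and no other route is given for them. Ceased-care outputs counted from cohort entry therefore mix never-starters with drop-outs, while the text around the occupancy plot reads the result as engagement lost. Outputs that begin at care-state entry, and those that measure initiation, are sound on this point.

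The size cannot be established from the article. The range of 27% to 93% rests on an assumed never-start share, a borrowed drop-out figure, and no death, loss of coverage, remission or censoring before the 194-day gap is completed. It shows what pooling can do, not what it will do here. For an exploratory study this is a worthwhile and inexpensive improvement; it does not threaten the design as a whole.

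**What to change.** 1. Add the initial state, with its direct exits to the terminal states, to the transition matrix. Each subcohort model then has 21 + 1 = 22 states.
2. Report ceased care from cohort entry split by whether any care state was entered. This can be done with a separate terminal state for SUD care never started (22 + 1 = 23 states), with ceased care then limited to episodes containing at least one care state. Alternatively, keep one terminal state and stratify the survival plot from index, the occupancy plot, the terminal-state percentages and the 1-year subgroup comparison.
3. Reword the opening sentence of Quantitative Study Population so that the cohort is patients identified with SUD, whether or not they go on to receive care.

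No new data are needed. The cost is slightly smaller counts per category and small edits to Table 2 and the Aim 1 text.

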#### Substance Use Data

Patient self-reported substance use frequency, patient self-reported SUD symptoms, and clinician-documented SUD diagnoses will be used to construct states. In the creation of initial states, diagnosis codes, service procedure codes, and revenue codes help determine whether a given health care visit was related to SUD. For instance, some initial states are defined by a new clinician-documented SUD diagnosis, while others are also defined to capture clinical workflows where patients are first identified as having substance use by the nature of a health screening (eg, substance use screening in primary care). Care states require an accompanying clinician-documented SUD diagnosis, unless the care state involves a procedure or medication that is solely indicated for SUD (eg, outpatient addiction treatment or disulfiram medication). The SUD remission state is captured using self-reported substance use frequency and SUD symptoms, and clinician-reported SUD remission diagnoses.

To obtain patient self-reported substance use frequency data, clinicians are prompted by the EHR to conduct annual screening with patients in primary care. During in-person visits, screenings are administered on paper or tablet by medical assistants, then entered into the EHR. In telephone or video visits, patients complete a questionnaire via an online patient portal. Validated substance use screening measures assess past-year alcohol, cannabis, and other drug use [32,39,40]. Patients with screening scores that are deemed to be at high risk for SUD are asked to complete a follow-up assessment for symptoms of SUD using the Alcohol Symptom Checklist and the Substance Use Symptom Checklist, respectively. These 11-item checklists capture symptoms of SUD that align with the 11 *DSM-5* diagnostic criteria [41]; the cutpoint of 2 or more symptoms is consistent with SUD. The checklists have demonstrated strong psychometric properties [42-44].

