**Figure 1. F1:**
[figure not shown]
Graphical representation of the multistate model. Notation: Subcohort: [*C*_*1*_; care states (*S*_*1*_,...,*S*_*15*_); discontinuation of care: *D*; SUD remission state: *R*; terminal states: (*T*_1_,...,*T_4_*); *t*: time, *p*: probability] The 3 dots connecting the states indicate that the depicted relationships are possible for the other states not shown in this figure. p: probability; SUD: substance use disorder; t: time.

We will adopt a semi-Markov assumption [59] under which transition intensities depend on only the duration that patients spend time in the current state before transitioning. This framework allows transition intensities to vary over time rather than assuming constant transition intensities as in the Markov framework. Time is defined as the duration since entry into a state, with the clock reset to 0 upon entry into the cohort and each subsequent state. At any time since entry into the initial state, a patient occupies 1 of the 21 states (17 transient states and 4 terminal states). Movements between states *j* and *k*
$\left(j,k=S_{1},\ldots ,S_{15},D,R,T_{1},\ldots ,T_{4}\right)$, are governed by a 21-by-21 matrix of transition intensities $q_{jk}(t,z(t))$, which is a function of time *t* and covariates z(t). Intensities capture the instantaneous probability of moving from state *j* to *k*.

Under the semi-Markov assumption, we will fit separate flexible parametric survival models [60,61] for each transition:

$\log\{q_{jk}(t,z(t))\}=s(\log(t)|\eta ,k_{0})+\beta^{T}z_{i}(t)$.

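### Ceased SUD care is defined by a narrower set of events than the care states, so an uncoded SUD-only procedure counts as care but does not stop a patient being classed as ceased

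*Protocol article*

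**What the plan says.** Three places in the protocol article bear on when a patient is in SUD care and when that care has ended.

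- **Substance Use Data** (under Data Used to Construct States) sets the entry rule: "Care states require an accompanying clinician-documented SUD diagnosis, unless the care state involves a procedure or medication that is solely indicated for SUD". It gives examples: "eg, outpatient addiction treatment or disulfiram medication".
- **States for the MSMs, Table 2**, defines the terminal state of ceased SUD care as "no medication fills or services with a qualifying SUD diagnosis for more than 194 days". The exception for SUD-only procedures and medications is not repeated.
- **Statistical Analyses, Aim 1**, in the paragraph on multiple incident events, describes a patient who has ceased care as "one who receives no SUD care for 194 days", with no diagnosis condition.

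Aim 1 also fixes the model structure. At any time "a patient occupies 1 of the 21 states (17 transient states and 4 terminal states)", and "patients cannot leave terminal states once they are entered in MSMs". Quantitative Study Population controls return to the analysis: a new incident event must occur "at a clinical encounter with no prior SUD indicators in the past 6 months".

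**The concern.** A multistate model needs states that exclude one another and rules that place each patient in exactly one of them. Here the rule that puts a patient into care and the rule that takes the patient out for good within the episode use different lists of qualifying events. An event can be on the first list and not on the second. A patient can then go on generating care-state visits while the ceased-care clock runs to its limit.

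Ceasing care is one of the four terminal states. It is the outcome in the worked RMST example (Table 5) and in the illustrative Figures 2 and 4. The text around Table 5 proposes to read a lower RMST as a sign that a care type tends to end in ceasing, and to direct coordination or staffing accordingly. If some care states depend more than others on uncoded SUD-only procedures, part of a difference in retention between states could come from the definition and not from patients leaving care.

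**Working it through.** No sample-size or power figure is involved. The check compares the rules event by event. The plan's own state count reproduces: 5 service types × 3 settings = 15 care states; 15 + 2 (discontinuation, remission) = 17 transient states; 17 + 4 terminal = 21.

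**Step 1: event types under each rule.** Table 2 can be read in two ways. In reading A the diagnosis condition applies to services only. In reading B it applies to fills as well. Uncoded means without an accompanying SUD diagnosis.

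| Event | Care state (Substance Use Data) | Resets ceased clock, reading A | Resets ceased clock, reading B |
|---|---|---|---|
| Service with SUD diagnosis | yes | yes | yes |
| Uncoded SUD-only procedure | yes | **no** | **no** |
| Uncoded fill of a SUD-only medication | yes | yes | **no** |
| Service with neither | no | no | no |

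The procedure row conflicts under both readings. The medication row conflicts only under reading B.

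**Step 2: what this does to one patient.** The visit schedule is assumed for illustration: SUD diagnosis on day 0, then an uncoded SUD-only procedure every 14 days to day 364.

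- Table 2, literal: the last resetting event is day 0, so the gap first exceeds 194 days on day 195 and the patient is ceased.
- Care-state visits after that fall on days 196, 210, …, 364: (364 − 196)/14 + 1 = 13 visits.
- With one shared list of qualifying events, the longest gap is 14 days and the patient is never ceased.

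**Step 3: what happens afterwards.** The terminal state closes this episode, but Aim 1 allows a later incident event to open another. An incident event needs a newly documented diagnosis or at least two checklist symptoms, with no SUD indicators in the previous 6 months. The article does not say whether an uncoded SUD-only procedure is such an indicator.

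- If it is, continuing treatment blocks re-entry.
- If it is not, the next coded visit could open a new incident episode in what was continuous care. It would add one to the count of prior incident events that Aim 1 uses as a covariate or stratification factor.

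**Step 4: threshold.** Table 2 requires more than 194 days, so ceasing is reached on day 195. The Aim 1 example says 194 days. The difference is one day, but it should be settled at the same time.

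**The case against.** The best reply is that the intended meaning can be seen elsewhere and the Table 2 cell is shorthand. Aim 1 speaks simply of no SUD care. The Table 2 footnote separates temporary discontinuation, itself a lack of SUD care, from ceasing by duration alone. Health Care Encounter Data lists procedure and revenue codes among the data used to build terminal states. A condensed article may leave code-level rules to a fuller document. Much of this stands as evidence of intent, and it shows which way to repair the text. It does not remove the conflict: both rules are stated, they differ, and a programmer who follows Table 2 as written gets the wrong result for these patients.

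The reply is also right that the conflict needs more than 194 days in which every SUD contact is an uncoded SUD-only procedure, and that nothing in the article suggests this is common.

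Three stronger readings are tempting and are not supported:

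- *Any prescription fill keeps an episode open.* Table 2 does not expressly limit fills to SUD medications, but the row concerns SUD care, and reading it to include unrelated prescriptions is strained. The wording needs clarifying and no more.
- *The patient is lost permanently and all later care is dropped.* Absorption is within the episode, and a new incident episode is possible if its criteria are met.
- *Specialty addiction treatment would look worse by a calculable amount.* Most such treatment is delivered by contracted programs and seen through claims, but the article does not say that those claims lack SUD codes. It gives no share of uncoded services, and no care state corresponds to specialty treatment as such, since states cross service type with setting.

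**Conclusion.** The point holds as a contradiction between stated definitions. For uncoded SUD-only procedures, the care-state rule and the ceased-care rule disagree however Table 2 is read. For uncoded fills of SUD-only medications, they disagree on one of two readings. Taken literally, the states are then not mutually exclusive within an episode, against the structure set out in Aim 1.

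The size of any bias cannot be stated from the documents and may be small. Its likely direction is clear: for care states that rely on the exception, RMST to ceasing would be too short and the probability of reaching the ceased state too high. This assumes that some patients do have such runs of uncoded contacts and that Table 2 is programmed as written. The study is exploratory and no terminal state is ranked above the others, so this is a definition to correct before the states are built. It does not undermine the design.

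**What to change.** Use one qualifying-event rule for being in care and for having left it:

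1. In Table 2, define ceased SUD care as more than 194 days with no event that would qualify for any of the 15 care states under Substance Use Data. That means no SUD-coded service and no procedure or medication solely indicated for SUD, whether or not a diagnosis accompanies it.
2. State that medication fills means fills that qualify as SUD care under that same rule.
3. Align the 194-day wording in the Aim 1 paragraph on multiple incident events with the Table 2 threshold of more than 194 days.

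With step 1 in place, no event type in the table above conflicts. The cost is about one sentence in Table 2 and a small wording change in Aim 1. The code lists are already needed to build the care states, and no further data are required.
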